### Therapist training, fidelity, and competence

Treatment will be delivered by two parent coaches. The coaches are part-time BA-level research staff, one of whom is bilingual in English and Spanish. The decision to use research staff as parent coaches was made in consultation with leaders of the residential facility, who wanted indication that the PW+ intervention was viewed favorably by parents before allocating substantial staff effort to the program. We specifically agreed to hire BA-level research staff with no clinical experience since these credentials are lower than those of program staff. Each coach will deliver both PW+ and SC sessions to prevent confounding of therapist effects. The study PI will train the two coaches. Parent coaches will review the PW computerized program and the manual for in-person sessions. Acting as a standardized patient, a study Co-Investigator with extensive experience treating adolescents with SUDs will role-play the four coaching sessions with each coach. These role plays will be recorded. The study PI will view these role plays, complete measures of therapist adherence and competence, and provide feedback to each counselor. Competency will be rated with six items that comprise the “General Therapeutic Skills” section of the Cognitive Therapy Rating Scale (CTRS) [70, 71]. A score >24 is the criterion to indicate competence. A 12-item adherence checklist for each coaching session has been developed. The coaches will be required to earn a satisfactory consensus CTRS score of >24 on three of four role plays and satisfactory adherence ratings (9 out of 12 elements) to be assigned an actual participant. Once the coaches are assigned participants, the PI will review and rate the first two tapes for adherence and competence. If ratings are satisfactory, the PI and a study Co-Investigator will collectively review 25% of tapes moving forward. The team will also rate 25% of SC sessions to ensure there is not drift between PW+ and SC sessions. The PI will meet weekly with the coaches for supervision focused on how to deliver PW+ with adherence, while flexibly tailoring content to each parent’s unique presenting concerns.

### Standard care (SC)

SC consists of the standard treatment elements offered to all residential patients at the partner residential center. Adolescents receive about 25 h of treatment per week. Before an adolescent is discharged (typical length of stay 6–10 days), parents are typically offered two family therapy sessions (which typically use a family systems approach and include case management planning). Adolescents receive four to 5 h of individual and group therapy sessions per day, consisting of psychoeducation and general skills building. Medication management is offered by a psychiatrist as needed. Prior to discharge, parents also receive standard discharge planning, which consists of either a referral to a new outpatient therapy provider or return to a prior outpatient therapy provider. As indicated, adolescents also receive referrals to a psychiatrist or local self-help groups. Post discharge, families are offered up to two check-in sessions to review the adolescent’s progress and troubleshoot any difficulties complying with the treatment plan.

### Adapted PW program

In addition to the SC elements, parents in the PW+ condition will receive the following elements: PW online modules, in-person coaching sessions, personalized texting, and an expert-moderated online parent board. All study materials will be translated into Spanish by a bilingual English and Spanish research staff member, and reviewed for accuracy by a Study Co-Investigator. Parents will be able to choose whether they prefer to receive materials in English or Spanish.

#### PW online modules

PW (Parenting Wisely/Ser Padres Con Sabiduría) is a self-administered, interactive, multimedia online program. PW contains video vignettes of ten common family problems (e.g., adolescent substance abuse, curfews, household chores, monitoring of friends, sibling conflict, improving in school, getting up on time, sharing technology, etc.). For each problem, parents progress through three activities: viewing of a video clip of a family struggling with the problem; selection of one of three possible solutions to the problem; and receipt of feedback about the solution selected. Feedback is presented via a video enactment of the selected solution and an explanation of the solution’s pros and cons. The goals of the feedback are to explain why ineffective solutions lead to problems and discuss how effective parenting solutions can prevent and resolve common family issues. Each vignette emphasizes six core behaviors: (1) problem solving; (2) limit setting; (3) praising; (4) effective communication through “I messages” and active listening; (5) supervision and monitoring, and (6) clear communication of adolescent’s behavioral expectations. Parents receive a parent workbook outlining all 10 vignettes, along with the potential problems and solutions. The workbook also contains a glossary of terms, sample behavior charts, and practice exercises. Parents create a unique login upon enrollment and can complete sessions at their own pace. Depending on the user’s speed and depth of use, the PW program typically takes between 3 and 5 h to complete.

#### Individual coaching sessions

Individual coaching sessions are designed to individually tailor the PW skills to each parent’s presenting concerns. The in-person coaching sessions correspond with four of the PW vignettes: substance use, limit setting, parental monitoring, and parental communication. The initial session is 60–75 min and consists of three sections: (1) rationale for parenting skills, (2) review of PW substance use module (in session), and (3) practice applying the skill to a current problem. Subsequent sessions follow the same outline and last 45–60 min, with active use of the PW program comprising about half the session. If parents introduce problems/complaints about their adolescent, the coach will first provide validation and then discuss how to apply a pertinent PW skill. Following discharge, the coach will also direct the parent to use the online parent board for additional support.

#### Text-based messaging

Following discharge, parents will receive text messages twice weekly for 12 weeks. The texts are intended to: (a) reinforce PW skills, (b) motivate continued PW usage, and (c) encourage participation in the online parent message board. In recognition of the ubiquity of text messaging in the general population [44] as well as in health-related research and clinical care [72], the PW developer has developed a set of text messages and videos to be delivered in conjunction with PW. In the open trial (Phase 1), it is possible that we will refine the text-messaging protocol (e.g., content, format, and frequency) based on feedback from parents during the exit interviews (described further below). One of the weekly messages will reinforce material taught in PW (e.g., a reminder statement about a parent strategy such as monitoring or communication) along with a link to a video clip enacting a core PW skill.

The second weekly text message will be encouragement for the parent to either practice PW vignettes or participate in the online parent message board. This protocol intentionally does not use interactive texting; instead, text messages will direct parents to ask questions via the parent board, an approach that we believe will ultimately be more transportable. Nonetheless, this limited application of texting is a potentially important ingredient to extending parents’ engagement in the parenting skills intervention, similar to the use of texting to provide support for smoking cessation [73] and to promote uptake of flu vaccinations [74] and outpatient clinic attendance [75].

#### Online parent board

Parents will be given access to a secure, expert-moderated website containing basic substance use and parenting skills information, links to sections of PW, as well as an interactive message board. Parents will be able to submit questions anonymously using the same unique login as for the PW program. All submitted questions will be reviewed by the project team to determine suitability for the board. Questions posted on the message board will be answered by the research team within 48 h. At the start of the treatment program, parents will be informed that the purpose of the parent online message board is to ask parenting related questions and not to request crisis support; requests for crisis support will be handled by the PI, a licensed clinical psychologist, and will not be shared on the message board. Answers to questions posted on the message board will direct parents to a specific PW module(s) most relevant to their parenting question. Participation on the message board will be encouraged for 12 weeks post-discharge, with the link to the board continually reinforced through text messages. The online message board will use the same login and password as the PW website, and the online message board will continually provide links to the PW website, to promote consistent use across platforms.

### Exit interviews

During the open trial phase, parents will complete exit interviews about their impressions of the PW+ program after the 6-week follow-up. Parent exit interviews contain questions about each aspect of the intervention, including the in-person sessions (e.g., number, content, format), text messages (e.g., content, frequency, format), and online message board (e.g., ease of access, content, format). Parents will also complete the 16-item Consumer Satisfaction Questionnaire (CSQ; [76]), which rates their satisfaction with treatment delivery, their adolescent’s treatment progress, and their ability to manage their adolescent’s problems. Parents rate 11 items along a 7-point scale (α = .91) and answer five open-ended questions about their experience in treatment. If more than one parent expresses the same concern with a protocol element (e.g., the frequency/number of in-person sessions, the frequency/content of texts, an aspect of the message board), then the element will be flagged for possible modification by the research team.

### Assessments

Parents and adolescents will complete a baseline assessment in-person shortly after their admission to residential treatment. Adolescents will be assured of confidentiality and a National Institute of Health Certificate of Confidentiality (CoC) will be obtained, as adolescent self-report use has shown reliability when confidentiality is assured [77–80]. The CoC will allow the research team to refuse to disclose names or other identifying characteristics of research participants in response to legal demands such as subpoena of records. Follow-up assessments will be conducted by an independent evaluator who is blind to condition. During the open trial, there will be follow-up assessment at 6 weeks post-discharge, while during the pilot randomized trial there will be three follow-up assessments at 6, 12, and 24 weeks post-discharge. Follow-up assessments will be scheduled in-person at the residential treatment center; if a parent no-shows more than twice for a follow-up assessment, then research staff will attempt to conduct the follow-up sessions at a location of the family’s choosing (i.e., home, school). The baseline assessment will be 1.5–2 h and the follow-up assessments will be about 1.5 h (see Table 3 for overview of measures).

**Table 3 Tab3:** Overview of protocol measures

Construct	Measurement/scale	Data obtained
Feasibility	Participation rates	Percent of parents who participate in the study
	Parent engagement	Number of coaching sessions attended, online usage of PW and parent message board (i.e., logins, sessions completed, page views, time spent), number of texts viewed
Acceptability	Withdrawal rates	Percent of parents who withdraw from study
	Exit interviews (open trial only)	Open-ended questions on perceptions of in-person sessions, text messages, computer program, and online message board
	CSQ	Satisfaction with treatment delivery and ability to manage their adolescent’s problems
Adolescent substance use	GAIN days of use	Days of alcohol use, marijuana use, and other drug use
	GAIN SFS	Averages percent of past 90 days during which there was use of alcohol, marijuana, or heavy drugs; intoxication; and failure to perform activities due to use
	Gain SUDS	Assesses substance use disorder symptoms in line with both DSM-IV and DSM-V criteria
	Biological markers	Saliva alcohol screens (12 h window) and 8 panel urine drug screens testing for marijuana, MDMA, cocaine, amphetamines, methamphetamines, opiates, oxycodone, and benzodiazepines
Adolescent high-risk behavior	GAIN risky sex	Series of items about risky sexual behavior over the past 90 days including number of partner, number of sexual contacts, and number of times had unprotected sex
	GAIN days legal	Days of legal involvement over the past 90 days
	GAIN days school	Days of school attendance/truancy over past 90 days
Parenting	PMQ	Parental monitoring and sources of parental monitoring
	PAC	Assesses positive and negative aspects of general parent-teen communication
	FAsTask video code	In vivo problem solving tasks focused on: limit setting; substance use norms; monitoring and listening

*CSQ* customer satisfaction questionnaire, *GAIN* global appraisal of individual needs, *SFS* substance frequency scale, *SUDS* substance use disorder scale, *PMQ* parental monitoring scale, *PAC* parent-adolescent communication scale

We selected adolescent measures to be as consistent with SC as possible. The residential center typically obtains a urine screen and administers a comprehensive adolescent interview to assess substance use and functioning across multiple life domains. We therefore combine biological markers with the Global Appraisal of Individual Needs—Quick (GAIN-Q3 [81]), a well-validated structured interview that assesses adolescents’ problems across several domains: substance use, school, mental health, physical health, risk behaviors, work, and sources of stress. The GAIN-Q3 substance use scales used in this protocol have demonstrated sound psychometric properties including internal consistency [82], high concurrence with the Timeline Followback Method [83], ability to predict SUD diagnoses made by blind raters (κ = .91) [84], and ability to predict substance-related problems as well or better than biometric markers [82]. The PI is a certified trainer of the GAIN family of instruments with experience analyzing GAIN data [85–88] and will train the independent evaluators.

To explore potential mediators of change, we augment the GAIN-Q3 with two brief measures of parental monitoring [89] and communication [90] (completed by both the parent and adolescent), as well as an in vivo parent-adolescent interaction task [91, 92]. The self-report measures have demonstrated good internal consistency and have correlated well with adolescent involvement in risky behavior, adolescent maladjustment, and family discord [89, 90], while the in vivo task has shown high inter-rater reliability [69]. These parenting measures will only be completed by those parents with have primary custody of their adolescent. If a parent loses custody post-discharge, parenting measures will not be administered (treating parent data as missing).

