### Study objectives and specific aims

The overarching goal of this protocol is to evaluate the feasibility, acceptability, and preliminary effectiveness of the adapted PW model (PW+) among parents of adolescents (age 12–17) preparing for discharge from acute residential SUD treatment. The project has two phases. In Phase 1, a pilot open trial tests the PW+ protocol with 10 parent-adolescent dyads. Feedback from residential staff, parents, and adolescents will be used to: (a) finalize a manual for adjunct individual coaching sessions, (b) develop coach training materials, and (c) refine the delivery and content of technology-assisted engagement strategies. During Phase 2, a pilot randomized controlled trial with 60 parent-adolescent dyads will evaluate the effectiveness of the PW+ intervention as an adjunct to residential standard care (SC). Combined, the activities in these two study phases will address three Specific Aims.

#### Specific aim 1

To examine the feasibility and acceptability (primary protocol outcomes) of the PW+ technology-assisted intervention among parents of adolescents in residential SUD treatment.

#### Specific aim 2

To examine the preliminary effectiveness of the PW+ technology-assisted protocol on adolescent substance use and associated high-risk behaviors (secondary protocol outcomes) over the first 24 weeks post-discharge.

#### Specific aim 3

To examine the preliminary effects of the PW+ technology-assisted on parental monitoring and communication (putative mediators of the intervention) over the first 24 weeks post-discharge.

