### Study enrollment and randomization

In accordance with institutional review board procedures at Brown University and Rhode Island Hospital, parents of all newly admitted adolescents will receive a Consent to Contact (CoC) form as part of the standard intake process at the residential center. Parents that sign a CoC form will then be contacted by research staff in one of two ways. If the adolescent is admitted Monday through Friday during normal business hours (which accounts for about 80% of new intakes), research staff located on site will immediately approach the parents and invite them to initiate the consent process. If the adolescent is admitted after hours or on weekends, research staff will contact the parents using the preferred contact information provided.

Parents will provide written informed consent and adolescents will provide written assent in separate private rooms at the residential center. If an adolescent chooses not to participate, the parent will be given general feedback that the family did not qualify so as to protect the adolescent’s privacy. Parents and adolescents may choose to conduct the informed consent process and all other study procedures in English or Spanish.

Parents will be given the choice whether to return for the baseline assessment or complete it immediately following informed consent. In the Phase 2 trial, randomization will occur within 24 h after the baseline assessment. Parent-adolescent dyads will be randomized to either SC or PW+ using urn randomization balanced on sex, severity of substance use, and preferred language (English vs. Spanish). Randomization will be conducted by a Co-Investigator, not involved with the assessment process, as soon as a parent consents to participate. Condition assignments will be placed in sealed envelopes and given to the independent evaluator. The evaluator will give parents their sealed envelope indicating that their treatment condition immediately after completion of the baseline assessment. If the parent is assigned to PW+, the evaluator will schedule the first in-person coaching session.

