### Retention procedures

Multiple steps will be taken to prevent attrition from the study follow-up assessments. First, during the baseline assessment, multiple sources of contact information will be recorded for parents and adolescents. In addition to extensive personal contact information, parents will provide detailed contact information of two friends or family members (“locators”) who can be contacted if research staff is unable to reach them. Follow-up reminders will be made via phone, text, and/or mail, depending on the parents’ preferences. The research team will meet weekly to review no-shows and outreach attempts, and discuss plans to connect with missing participants. Parents and adolescents will each receive an escalating schedule of compensation in the form of gift cards for completing the baseline ($40) and three follow-up assessments ($50, $50, $60, respectively).

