#### Primary outcomes: feasibility and acceptability

In the open trial and randomized controlled pilot trial, feasibility will be examined via enrollment rates (>80%) and indicators of parental engagement, with the following preliminary targets: attendance of >1 coaching sessions pre-discharge and >1 sessions post-discharge for >75% of parents, and online usage patterns of 2+ PW logins, 2+ parent board logins, and 1+ h logged in for >75% of parents. Criteria for acceptability include withdrawal rates (<20%), satisfaction ratings (>80% of items on the CSQ rated “agree” or “strongly agree”) and positive feedback from exit interviews with parents and therapists. Criteria will be finalized based on parent and staff feedback in Phase 1.

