#### Sample size and power

The study will recruit 60 participants for the randomized trial. Estimating that 15–20% may be lost to follow-up, there will likely be 50 participants with complete parent-adolescent data. We will use these participants to make judgments regarding feasibility and acceptability. Effect size estimates in prior PW studies have ranged from small to very large; the only study conducted among adolescent substance users found small to medium effects, but unlike this application, that study did not offer in-person support or an online parent board (supports that may contribute to larger effect sizes). Furthermore, even small effects, if obtained by delivering content electronically via a highly scalable platform that can reach large numbers of parents, can have significant public health implications. Despite issues with effect size stability in small samples [99], a small to medium effect paired with high levels of feasibility and acceptability would therefore be an indication that the adapted PW intervention should be tested in a larger trial. Based on the detected effect size, post hoc power analyses will be conducted to determine the number of parents required for a fully powered trial. For instance, for power of .8, a small effect size (d = .3) would require a sample of 175 per group, while a medium effect size (d = .5) would require a much smaller sample of 64 per group.

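### The withdrawal part of the acceptability outcome counts parents who leave the study: it misses those who stop PW+ but stay in follow-up, and it is not restricted to PW+ parents

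*Protocol article*

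**What the plan says.** Specific aim 1 is "To examine the feasibility and acceptability (primary protocol outcomes) of the PW+ technology-assisted intervention", so the object of the acceptability judgement is the intervention.

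The analysis section on primary outcomes gives the threshold: "Criteria for acceptability include withdrawal rates (<20%), satisfaction ratings" and positive exit-interview feedback. Table 3 (Assessments) defines the withdrawal measure as "Percent of parents who withdraw from study". Neither place names an arm, and neither mentions stopping the intervention as distinct from leaving the study.

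On the sample: "The study will recruit 60 participants for the randomized trial", and "Parent-adolescent dyads will be randomized to either SC or PW+ using urn randomization". The allocation ratio is not stated. The Sample size and power section expects about 50 participants with complete data after 15–20% loss, and says that feasibility and acceptability will be judged on those participants, without separating the arms.

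The engagement targets (coaching attendance, PW and message-board logins, time online, each for more than 75% of parents) appear under feasibility. The same section says that the criteria will be finalised after Phase 1.

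**The concern.** The measure and its target differ in two ways.

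**Event.** A parent can reject coaching, texts and the message board and still attend assessments. That parent has not withdrawn from the study. Assessments are paid: "Parents and adolescents will each receive an escalating schedule of compensation in the form of gift cards", amounting to $40 + $50 + $50 + $60 = $200 for each of parent and adolescent. Locators and weekly review of no-shows further support attendance. These are ordinary and proper retention measures for all participants, but they mean that a study-withdrawal rate mainly describes assessment retention. This applies in both phases and does not depend on how the denominator is read.

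**Denominator.** In Phase 2, SC parents never receive PW+, so their remaining in the study says nothing about its acceptability. If they are in the denominator, a low SC withdrawal rate hides a higher one in PW+.

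What is at stake is one of the signals for a larger trial. The Sample size and power section treats a small to medium effect, paired with high feasibility and acceptability, as grounds to go on.

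**Working it through.** The article derives no figure for the 20% limit, so there is none to reproduce for it. The neighbouring figure can be checked: 60 × 0.85 = 51 and 60 × 0.80 = 48, which bracket the stated 50 completers.

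**Inputs.** From the document: 60 randomised dyads, two arms, limit below 20%, engagement targets for more than 75% of parents. Assumed: 30 parents per arm, and the arm-specific withdrawal rates, for which the document gives no values.

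**Step 1: counts that pass.**
- Pooled: the largest k with k/60 < 0.20 is 11 (11/60 = 18.3%).
- PW+ only: the largest k with k/30 < 0.20 is 5 (5/30 = 16.7%).

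**Step 2: highest PW+ rate compatible with a pooled pass.**
- All 11 in PW+: 11/30 = 36.7%. If urn randomisation gave 25 or 35 PW+ parents: 11/25 = 44% or 11/35 = 31%.
- With 2, 3 or 4 SC withdrawals: 9/30 = 30%, 8/30 = 26.7% or 7/30 = 23.3%.

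**Step 3: probability of passing.** Let X ~ Bin(30, p) be withdrawals in PW+ and Y ~ Bin(30, q) those in SC. Pooled pass = P(X + Y ≤ 11); PW+-only pass = P(X ≤ 5).

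| PW+ rate p | SC rate q | Pooled pass | PW+-only pass |
|---|---|---|---|
| 30% | 0% | 0.84 | 0.08 |
| 30% | 5% | 0.65 | 0.08 |
| 30% | 10% | 0.45 | 0.08 |
| 30% | 15% | 0.27 | 0.08 |
| 25% | 10% | 0.65 | 0.20 |
| 20% | 20% | 0.45 | 0.43 |

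The gap comes from SC withdrawing less often than PW+. In the last row, where the rates are equal, it almost vanishes.

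**Step 4: parents who stop PW+ but stay in follow-up.** Each adds zero to the count. This criterion alone therefore sets no upper limit on discontinuation of PW+, whichever denominator is used.

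**Step 5: how far the engagement targets compensate.** More than 75% of 30 requires at least 23 parents (22/30 = 73.3% fails; 23/30 = 76.7% passes), so at most 7 may fall short. Suppose that every withdrawing PW+ parent leaves before meeting the targets and every other PW+ parent meets them. The probability of passing both pooled withdrawal and engagement, P(X ≤ 7 and X + Y ≤ 11), is then 0.28 for 30%/5% and 0.47 for 25%/10%, down from 0.65 in each case. Parents who leave after meeting the targets are not caught by this check.

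**The case against.** The strongest reply has four parts.

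1. **Pooling is nowhere stated.** Aim 1 concerns PW+, and the paragraph with the 20% limit uses unqualified "parents" for targets that only PW+ parents can meet, such as PW logins. The withdrawal limit may be meant the same way. The sentence in Sample size and power does not settle it: it also covers feasibility, where pooling makes no sense, and participants with complete data cannot by themselves supply a withdrawal rate. This stands. Pooling is the literal reading of Table 3 taken with that sentence, not an explicit rule; otherwise the denominator is simply unspecified. The event problem is unaffected, because Table 3 names the study and not the intervention.

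2. **Other criteria would notice.** Satisfaction ratings are also part of acceptability, and the engagement targets would expose many early drop-outs (step 5). This stands in part. Ratings come only from parents who respond, Table 3 confines exit interviews to the open trial, and the engagement targets sit under feasibility. A reader might infer that PW+ could be declared acceptable, or taken to a full trial, despite wide rejection. The document does not support that: acceptability has several criteria, and progression also depends on feasibility and the effect estimate.

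3. **The criteria are provisional.** True, and so the correction is timely. All 10 Phase 1 parents receive PW+, however, so Phase 1 cannot itself reveal dilution by SC parents.

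4. **The rates are assumed.** Also true. The document gives only 15–20% overall loss to follow-up. The probabilities show what could happen, not what is expected.

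**Conclusion.** The concern holds for the withdrawal component. As defined, it measures leaving the study, does not count parents who stop PW+ but remain in follow-up, and is not restricted to PW+ parents. The first defect follows directly from Table 3 and applies in both phases. Dilution applies only to Phase 2 and rests on the pooled reading, an assumed 30 parents per arm, and a lower withdrawal rate in SC than in PW+. Under those conditions a PW+ withdrawal rate of up to 36.7% can pass. At a true 30% in PW+, the chance of passing is 0.27 to 0.84 for SC rates from 15% down to 0%, against 0.08 on PW+ parents alone.

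This should be fixed, but it is one part of a multi-part pilot judgement. It does not by itself invalidate the acceptability outcome or the decision to proceed.

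**What to change.** When the criteria are finalised after Phase 1 and before Phase 2 is judged:

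- Define the acceptability measure as the percentage of all parents allocated to PW+ who ask to stop PW+ or withdraw from the study during the 12-week post-discharge PW+ period, counting each parent once. Apply the limit of below 20% to it.
- Report the 10 open-trial parents separately, using the same definition.
- Report study withdrawal by arm as a separate retention measure.

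The cost is a change of wording, one data field for a request to stop PW+, and lower precision, since the denominator falls from 60 to about 30. With 30 parents at most 5 may be counted. The criterion becomes harder to meet: at a true PW+ rate of exactly 20% it would be met with probability 0.43.
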